### Eligibility criteria {10}

Researchers will conduct eligibility screening based on inclusion and exclusion criteria. All participants should sign an informed consent form after qualification confirmation.

Inclusion criteria:Male or female patients between 18 and 75 years of age;Right-handed;Patients who meet the diagnostic criteria for vascular cognitive impairment reported in the Guidelines from the Vascular Impairment of Cognition Classification Consensus Study [9] and the Chinese vascular cognitive impairment guideline 2019 [10];The patient should have a clear consciousness and stable vital signs. They should also be able to express themselves and understand instructions to a certain extent. At least one limb should be movable without any issues, and the patient must be willing to participate in cognitive assessments and related training actively;The patient had no cognitive impairment before the onset of the disease but had mild to moderate cognitive impairment after the stroke. They had a primary school education level or above, with a score of 9 < MMSE < 27 and a score of 9 < MoCA < 26;No mental illness, no severe aphasia or hearing comprehension disorders; andVoluntary participation and signing the informed consent (signed by the patient or the authorized person).

Exclusion criteria:Cognitive impairment due to primary or secondary neurological disease, such as normal cranial pressure hydrocephalus, frontotemporal dementia, Parkinson’s disease, multiple sclerosis, encephalitis, and delirium;Accompanied with severe mental, intellectual disabilities, or visual and auditory dysfunction, unable to cooperate in completing various functional evaluations;Cognitive impairment due to depression, schizophrenia, bipolar disorder, psychotic disorder, vitamin D deficiency, toxicosis, or else systematic diseases;Drug/alcohol abuse/dependence within the last 3 months of the first recognition of impairment;rTMS treatment contraindications such as epilepsy patients, pregnant or lactating women, or with a metal or electric implanted device (e.g., deep brain stimulator, ventriculoperitoneal shunt, aneurysm clip, pacemaker, cochlear, surgical staples on the scalp);MRI contraindications (such as metal implants or claustrophobia); andParticipating in concurrent pharmacological or nonpharmacologic treatment research.

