### Outcomes {12}

This study measures the effectiveness of rTMS treatment on cognitive ability. Two primary assessments will be conducted, the Montreal Cognitive Assessment Beijing Version (MoCA-BJ) and the Mini-Mental Status Examination (MMSE). In addition, secondary assessments such as the modified Barthel index (MBI), Trail-Making Test (TMT), digital span test (DST), transcranial Doppler (TCD) examination, and serum BDNF and VEGF levels will also be conducted. All assessments will be done twice, pre-treatment (baseline) and post-treatment. A trained neuropsychologist will conduct all cognitive assessments without informing the participants’ cognition status.MoCA-BJ. The MoCA-BJ scale is one of the Chinese versions of the Montreal Cognitive Assessment used to assess general cognitive function [13], which has high sensitivity and specificity for screening cognitive impairment from patients with stroke [14]. The cognitive function was evaluated through alternating connections, drawing cubes, drawing clocks, naming, retelling, subtracting seven from 100, and directional ability. This scale was developed based on MMSE, with a score of 30 points and ≥ 26 points representing normal cognition [15]. A patient’s cognitive function is better if their score is higher.MMSE. The MMSE is a quick and easy cognitive function screening tool commonly used in clinical settings. It takes about 10 min to complete and consists of a single-page, 30-point test that assesses various cognitive domains including memory, attention, and language. A higher score indicates better overall cognitive function, with a score of 27–30 indicating normal function, 21–26 indicating mild impairment, 10–20 indicating moderate impairment, and 0–9 indicating severe impairment [16].TMT(Chinese version). In the TMT-A section, connect the numbers from 1 to 25. TMT-B includes numbers in square and circular shapes, requiring participants to arrange the two forms alternately when connecting numbers in sequence. The scoring criteria are the time taken to complete TMT-A and TMT-B, as well as the interference amount (TMT-B time consumption minus TMT-A time consumption) [17]. This tool is commonly used for diagnosing visual attention, executive function, and processing speed in neuropsychological diseases [18, 19].ADL. The primary activities of daily living are assessed with the modified Barthel Index (MBI) [20], which is used to evaluate individual self-care performance and derived from the Barthel Index. In this study, we used the Chinese version of MBI [21]; it also consists of ten items: personal hygiene, bathing, feeding, toileting, stair climbing, dressing, bowel control, bladder control, ambulation or wheelchair and chair-bed transfer with total 100 scores indicating completed independence. A higher score on the MBI indicates superior independent living ability [22].DST. The scale can be divided into digit span forward (DSF) and digit span backward (DSB), each of which consists of two sets of 2-digit to 10-digit tables. The test begins with item 1 and is stopped after two incorrect attempts. The total score of the DSF and DSB indicates the participant’s attentional functioning, with a higher score indicating better function. A score of less than 5 suggests impaired attention function [23].TCD. According to the latest epidemiological survey, cerebrovascular disease and its risk factors are significant contributors to cognitive decline. By managing these risk factors, it is possible to delay cognitive decline [24]. TCD can assess large vascular lesions and cerebrovascular function, which can provide a basis for early diagnosis and treatment of PSCI [25]. The main indicators for assessment are the average blood flow velocity (Vm), pulsatile index (PI), and resistance index (RI) of the patient’s middle cerebral artery, which measure cerebral hemodynamic changes.Blood sampling. Serum samples will be obtained to analyze BDNF and VEGF levels at baseline and post-treatment. Peripheral venous blood (5 ml) will be collected from 7:00 am to 9:00 am in a climate-controlled room following overnight fasting [26]. The blood was then centrifuged to separate the serum and stored at -80℃ in a refrigerator. Serum levels of BDNF and VEGF will be measured using enzyme-linked immunosorbent assay (ELISA) kits. The steps were followed according to instructions [27]. All samples will be measured by the same technician who is blinded to the patient treatment status. All samples will be evaluated in duplicate and averaged.

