## Statistical methods

### Statistical methods for primary and secondary outcomes {20a}

Statistical analysis will be conducted using SPSS version 25.0 and Microsoft Excel 2016 software.

Measurement data (e.g., MoCA BJ, MMSE, TMT, DST, MBI, BDNF, and VEGF levels in serum, TCD) were statistically described by mean ± standard deviation (*x* ± *s*); count data (such as stroke type, hemiplegic side, and stroke risk factors) were described by frequency (*n*) and percentage (%). The measurement data were first tested for normality, and those not conforming to the normal distribution were expressed by M (P25, P75) and analyzed by Kruskal–Wallis H test; the data conforming to the normal distribution were expressed by *x* ± *s*, one-way analysis of variance was used for comparison between multiple groups, LSD-t-test, and paired *t*-test was used for patients before and after treatment. All test levels were significant at *α* = 0.05 and *P* < 0.05.

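### The between-arm test of MMSE and MoCA-BJ carries no baseline covariate, although both scores are measured at baseline; this costs precision, not validity

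*Protocol article*

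**What the plan says.** Outcomes {12} names the primary outcomes: "Two primary assessments will be conducted, the Montreal Cognitive Assessment Beijing Version (MoCA-BJ) and the Mini-Mental Status Examination (MMSE". The same section fixes the schedule: "All assessments will be done twice, pre-treatment (baseline) and post-treatment". A baseline value of each primary score is therefore part of the planned data for every patient.

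Statistical methods {20a} names the tests. After a normality test, normal data go to the branch "one-way analysis of variance was used for comparison between multiple groups, LSD-t-test", and non-normal data are "analyzed by Kruskal–Wallis H test". The only stated use of baseline in a test is within patients: "paired *t*-test was used for patients before and after treatment". The significance rule is "All test levels were significant at *α* = 0.05 and *P* < 0.05".

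The section does not say whether the ANOVA or Kruskal–Wallis test is applied to the post-treatment score or to the change from baseline. Implementation {16c} gives 19 patients to each arm from ranked random numbers, and neither it nor Sequence generation {16a} describes stratification.

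**The concern.** The third objective is to find out whether dual-target stimulation does better than single-target. That is a contrast between arms. The paired tests look at each arm separately and cannot answer it, so the answer rests on the unadjusted ANOVA or Kruskal–Wallis test.

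Eligibility {10} admits patients "with a score of 9 < MMSE < 27 and a score of 9 < MoCA < 26", that is MMSE 10 to 26 and MoCA 10 to 25. Patients can differ widely at entry, and with 19 per arm chance alone can leave arms visibly different. If entry scores predict follow-up scores, a comparison without a baseline covariate leaves that predictable variation in the error term and leaves part of any chance imbalance in the estimated effect. The contrast of most interest is between two active arms in a small trial, where lost precision is hard to afford.

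**Working it through.** **Inputs from the protocol article.** 1:1:1 allocation, 19 per arm, total 57, 20% expansion for dropout, α = 0.05 (two-sided assumed). Sample size {14} gives no effect size, SD or power, so 57 cannot be reproduced in full. The dropout step is consistent with 15 completers per arm: 15/(1 − 0.2) = 18.75, rounded up to 19, and 3 × 19 = 57.

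**Assumed inputs (not in the article).** Correlation r between baseline and post-treatment score of 0.3 to 0.8; equal SD at both times; for power only, a 3-point MMSE difference and SD of 4, so 0.75 SD.

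**1. Chance imbalance at baseline.** The standard error of a difference between two arm means is √(2/19) = 0.324 SD. P(|difference| > 0.5 SD) = P(|Z| > 0.5/0.324) = P(|Z| > 1.54) = 12%. By simulation, the probability that at least one of the three pairs differs by more than 0.5 SD is 27%.

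**2. How imbalance reaches the estimate.** For a baseline difference D, the unadjusted contrast is shifted by rD on post-scores and by −(1 − r)D on changes. With D = 0.5 SD and r = 0.7 these are +0.35 SD (1.4 points at SD 4) and −0.15 SD (−0.6 points).

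**3. Information lost against ANCOVA.** Relative to post-score ANOVA, the variance of an arm difference is 1 − r² for ANCOVA and 2(1 − r) for change scores. The loss is therefore r² if post-scores are analysed, and 1 − (1 − r²)/[2(1 − r)] = (1 − r)/2 if changes are analysed.

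**4. Power for one pairwise contrast, 19 per arm.** Non-central t with the error pooled over three arms. For post-scores the non-centrality is 0.75/√(2/19) = 2.31 on 54 df. ANCOVA uses 53 df, variance factor 1 − r², and a small allowance, 1 + 1/52, for estimating the slope.

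| Assumed r | Loss, post-scores | Loss, changes | Power, post-score ANOVA | Power, change ANOVA | Power, ANCOVA |
|---|---|---|---|---|---|
| 0.3 | 9% | 35% | 62% | 48% | 65% |
| 0.5 | 25% | 25% | 62% | 62% | 74% |
| 0.7 | 49% | 15% | 62% | 83% | 88% |
| 0.8 | 64% | 10% | 62% | 95% | 96% |

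With 15 completers per arm, post-score ANOVA has 52% power and ANCOVA 55%, 63%, 79% and 91% in the same order of r. A simulation of 20,000 trials at r = 0.7 and 19 per arm gave a variance ratio of ANCOVA to post-score ANOVA of 0.516, against 0.51 from the formula.

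**The case against.** The strongest reply is that nothing here is invalid. Under randomisation the unadjusted ANOVA is unbiased on average and keeps its type I error, and a 12% chance of a 0.5 SD imbalance in a given pair is ordinary for arms of 19. This stands, and it limits the point to precision and to the estimate conditional on the imbalance that happens to occur.

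A second reply is that the ANOVA may be run on changes, in which case baseline is used after all. This also stands as a possibility. A reader might infer from the wording that baseline is ignored altogether, but the article does not settle it. ANCOVA is the more precise choice under either reading, though at r = 0.8 the power gain over change scores is only about one point.

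A third reply is that the size depends on figures the article does not give. That is so. A reader might infer that half the information is wasted, or that ANCOVA is worth 57/0.51 = 112 patients. Both are the case of r near 0.7 with post-scores; they are neither a bound nor a property of this trial. Truncating entry scores by eligibility tends to lower r.

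Two extensions are tempting and unsupported. The article lists hemiplegic side among "count data (such as stroke type, hemiplegic side, and stroke risk factors" and others, as descriptive data. Because the DLPFC target is always left and the M1 target ipsilesional, side decides whether the two targets share a hemisphere. That is a question of arm-by-side interaction, which a main-effect covariate would not address, and nothing in the article shows that side predicts cognition. Nor does it give any basis for log-transforming BDNF and VEGF.

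Finally, an analysis plan not shown might add detail. But the article names its between-arm tests, so the point concerns a stated method and not an omission.

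**Conclusion.** The point holds as a matter of efficiency. The stated between-arm tests have no baseline covariate although the covariate is collected, and the analysed variable is left open. If post-scores are compared, the loss against ANCOVA runs from 9% to 64% over r of 0.3 to 0.8; if changes are compared, from 25% down to 10% over r of 0.5 to 0.8. The power gains rest on an assumed 3-point difference, SD of 4 and two-sided 0.05, and are small if r is low. The imbalance figures need only the arm size, simple randomisation and approximate normality of the arm means. It should be fixed because it is free, but the trial's inference does not fail without it.

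**What to change.** In Statistical methods {20a}, make the prespecified between-arm analysis of MMSE and MoCA-BJ, and of the other scored outcomes, an ANCOVA of the post-treatment score on arm plus the baseline value of the same score. Report adjusted pairwise differences with 95% confidence intervals. Let this replace both the one-way ANOVA and the unadjusted Kruskal–Wallis branch, and keep the paired t-tests as description only. Naming the post-treatment score as the response also settles which variable is analysed.

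The cost is one degree of freedom and a rewritten paragraph, since the normality-test branch has to be reworded too. It needs no new patients, measurements or software: the SPSS version already named fits the model. The change should be made before anyone sees outcome data by arm.

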### Interim analyses {21b}

There are no interim analyses planned.

### Methods for additional analyses (e.g., subgroup analyses) {20b}

There are no subgroup analyses planned.

### Methods in analysis to handle protocol non-adherence and any statistical methods to handle missing data {20c}

We will evaluate the loss of primary outcome data through intention-to-treat analysis. Missing data will be reduced to a minimum by using the multiple imputation.

### Plans to give access to the complete protocol, participant-level data and statistical code {31c}

The corresponding author can make the datasets used and analyzed during the current study available upon reasonable request and in agreement with China’s research collaboration and data transfer guidelines.

## Oversight and monitoring

### Composition of the coordinating center and trial steering committee {5d}

This trial is overseen by a team consisting of a principal investigator who is responsible for both prosecution and medical care of patients, a data manager who ensures data capture and quality, a study coordinator who handles registration and study visits, and a study physician who identifies potential recruits and ensures proper follow-up. The team meets every Thursday, but there is no trial steering committee or stakeholder/public involvement group involved.

### Composition of the data monitoring committee, its role and reporting structure {21a}

To ensure the integrity of the study, a Data Monitoring Committee (DMC) is necessary to maintain the blinding of the researchers and physicians. Additionally, a safety officer with expertise in adverse reactions will be designated to oversee the study’s safety. In the event of any adverse reactions, the safety officer will be notified within 24 h.

### Adverse event reporting and harms {22}

Adverse events (AE) during or ≤ 1 h after the session, including headache, scalp dysesthesia/paresthesia at the stimulation site, muscle pain of temporal or neck muscles, and seizures, will be documented after each treatment session and during the whole treatment period. All adverse events would be reported to the DMC and relevant regulatory bodies. In addition, we will also report specific information on the expectedness, seriousness, severity, and causality of adverse events.

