### Intervention description {11a}

#### rTMS protocol

The rTMS treatment uses a magnetic stimulator with an 8-shaped coil (MagProX100, Denmark). Participants were divided into three groups: the sham stimulation group, the single-target stimulation group, and the dual-target stimulation group. After recruiting PSCI patients, they were randomly assigned to one of three groups for 20 treatment courses (4 weeks, 5 consecutive days, and 2 days off per week). During the sham stimulation, the “8” shaped coil was placed at a 90° angle to the scalp. The rTMS treatment of the three groups will be completed by a qualified therapist with over 5 years of work experience from the Neurocontrol Room of Shanghai Herson Rehabilitation Hospital.

The detailed information on parameters and grouping were as follows:Group 1: sham rTMS over left DLPFC+ ipsilesional M1Group 2: left DLPFC+sham rTMS over ipsilesional M1Group 3: left DLPFC+ ipsilesional M1Left DLPFC: 10 Hz, 80% RMT, 2000 pulses (5s×40 trains,25s interval)Ipsilesional M1: 10 Hz, 80% RMT, 1200 pulses, (2s×60 trains, 8s interval)

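### The adverse-event sentence limits events to within 1 hour of a session but also promises recording throughout treatment; the two must be reconciled

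*Protocol article*

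**What the plan says.** The Protocol article's section on adverse event reporting and harms {22} opens with the events of interest, "Adverse events (AE) during or ≤ 1 h after the session". It gives examples: headache, abnormal scalp sensation, temporal or neck muscle pain, and seizure. The sentence ends by saying that these "will be documented after each treatment session and during the whole treatment period". The next sentence is unqualified: "All adverse events would be reported to the DMC and relevant regulatory bodies".

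The section on the data monitoring committee {21a} also sets no limit on time of onset: "In the event of any adverse reactions, the safety officer will be notified within 24 h".

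The discontinuation criteria {11b} include worsening symptoms, again without reference to when the worsening begins.

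**The concern.** The 1-hour qualifier is attached to the events themselves, so grammatically it settles which events count. The later phrase about the whole treatment period is attached to the documenting, so it can be read as saying only when recording takes place. On that reading an event that starts several hours after a session, or on one of the two days off each week, is not an event to be documented, even though recording continues for four weeks.

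This does not sit well with the rest of the plan. The safety officer is to hear of any adverse reaction, and a patient may stop because of worsening that begins between sessions. Both can involve events that fail the 1-hour definition. Notification also depends on an event having been noticed and recorded, so the notification rule does not settle what is collected.

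At stake is the completeness of the safety record, and whether two members of staff would record the same event in the same way. The primary outcomes, sample size, power and significance level are not affected.

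**Working it through.** **Step 1: the texts side by side.**

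| Place | What it governs | Limit on time of onset |
|---|---|---|
| {22}, start of first sentence | which events | during the session or up to 1 h after it |
| {22}, end of first sentence | when they are documented | after each session and throughout treatment |
| {22}, second sentence | reporting to the DMC and regulators | none stated |
| {21a} | notice to the safety officer | none stated (24 h is the time allowed for notice) |
| {11b} | discontinuation for worsening symptoms | none stated |

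The first sentence of {22} allows two readings.
- *Narrow:* only events within the 1-hour window are recorded, and this is repeated over four weeks.
- *Broad:* session-linked events are recorded after each session, and events are also recorded throughout treatment.

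**Step 2: session length, from the rTMS protocol section.** The left DLPFC block is given as "2000 pulses (5s×40 trains,25s interval" and the M1 block as "1200 pulses, (2s×60 trains, 8s interval", both at 10 Hz. The plan's own pulse counts check the timings (pulses = frequency × train length × trains):
- DLPFC: 10 × 5 × 40 = 2000, as stated.
- M1: 10 × 2 × 60 = 1200, as stated.

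Duration = trains × (train + interval):
- DLPFC: 40 × (5 + 25) s = 1200 s = 20 min.
- M1: 60 × (2 + 8) s = 600 s = 10 min.
- Session: 30 min = 0.5 h, with no set-up time counted (none is stated).

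**Step 3: time inside the 1-hour windows.** The schedule is "20 treatment courses (4 weeks, 5 consecutive days, and 2 days off per week", so there are 20 sessions.
- Covered: 20 × (0.5 + 1) h = 30 h.
- Treatment period: 28 × 24 h = 672 h.
- Inside: 30 / 672 = 4.5%. Outside: 95.5%.

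**Step 4: sensitivity to the assumptions.**

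| Assumption | Covered (h) | Period (h) | Outside |
|---|---|---|---|
| 28 days | 30 | 672 | 95.5% |
| 26 days (first to last treatment day) | 30 | 624 | 95.2% |
| Start of first session to 1 h after the last (25 × 24 + 1.5) | 30 | 601.5 | 95.0% |
| 28 days, 30 min extra per session | 20 × 2 = 40 | 672 | 94.0% |
| 28 days, stated interval taken to include the train (40 × 25 s + 60 × 8 s = 24.7 min) | 28.2 | 672 | 95.8% |
| Only the 20 treatment days | 30 | 480 | 93.8% |

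Across all the combinations tried, 93% to 96% of the calendar period lies outside the windows, or 92% to 94% if only treatment days are counted.

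**Step 5: what this does and does not measure.** These are shares of clock time on the narrow reading. Turning them into a share of events needs the distribution of onset times, which the document does not give. On the broad reading the share of the treatment period left uncovered is 0%.

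**The case against.** A reader might infer that later events are simply not captured for about 95% of treatment. The document does not support that as a statement of fact. The sentence goes on to promise documentation throughout treatment. If that meant no more than repeating the after-session recording, the words would add little, so a second, continuous collection period is a natural reading. The unqualified wording on reporting in {22} and on notification in {21a} points the same way.

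A reader might also take 95% as the proportion of events lost. It is not. It would hold only if onset were spread evenly over every hour, and several of the listed examples are local effects linked to the session.

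Nor can it be said that the dual-target arm would lose most. All three arms receive two-site sessions with sham substituted, so if sham follows the same timings the window is the same in each. The article lists no safety outcome and no between-arm test of harms, so no planned comparison is shown to be distorted. Patients are under care at the hospital, which makes a serious event less likely to go unnoticed.

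Finally, some operational detail of collection may sit in a full protocol or case record form that is not shown.

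All of this stands as a limit on the size of the point. It does not remove the inconsistency. On the broad reading the 1-hour qualifier does no work and should not define the events; on the narrow reading it conflicts with the sections around it. The sentence needs correcting either way, and this is a rule the article states, not a detail it leaves out.

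**Conclusion.** The point holds as an internal inconsistency in the window for collecting adverse events. Applied literally, the 1-hour qualifier would exclude events of later onset, and the windows would then span about 30 h of 672 h (4.5%). This rests on 20 sessions of about 30 minutes, a 28-day period and no set-up time, and it changes little under the alternatives tried.

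The number of events affected cannot be derived from the document, and it is zero within treatment if the broad reading was intended. A differential loss between arms is conjecture. The matter is worth correcting because it concerns safety data and the remedy is small.

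**What to change.** Reword the first sentence of {22} so that being within 1 hour of a session is no longer a condition for recording, and bring it into line with {21a}. State that all adverse events are collected from the first session to the W5 assessment, each with its time of onset, by asking at the start of the next session and again at W5. Naming W5 as the end also settles the interval between the last session and that visit, which wording confined to the treatment period leaves open. Keep onset during the session or within 1 hour as a subcategory for reporting, so that session-linked effects can still be shown separately.

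The cost is about one extra question per session and slightly more events to process. The per-session record card described under adherence {11c} could carry the question, on the assumption that it can be extended; the article describes it only as a treatment record. No change to sample size, visits or outcome analysis follows.
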